## INTRODUCTION

### Background

Peripheral nerve blocks are frequently used as part of a multimodal pain treatment. The advantages of nerve blocks are, in addition to pain relief, reduced morphine consumption and consequently less morphine-related side effects such as nausea, vomiting and sedation. Nerve blocks can be performed either as a single (bolus) or as a continuous infusion using perineural catheters. The limitation of single-shot blocks is the relatively short duration. Compared to the catheter-based solutions single-shot blocks may be associated with a lower risk of infection, are considered to be less complicated to perform and can easily be used for outpatients (1, 2).

In order to prolong the effect of single-shot blockades, attempts have been made to add various adjuvants for local anesthetics with varying success. Several studies have shown that clonidine prolongs the duration of a single-shot nerve block compared to placebo (3-20), but it is unclear whether this effect is exerted via a systemic or local mechanism (3-5, 21-23). We wish to investigate whether perineural administration of clonidine prolongs the duration of a ropivacaine nerve block, when controlling for systemic effects.

Our group has validated different methods that can be used to assess the duration of sensory block, and found that the following methods can estimate the duration with high precision: temperature discrimination test with an alcohol swab, pin-prick, warmth detection threshold, WDT, and heat pain detection threshold, HPDT, as well as pain during tonic heat stimulation of the skin (24).

Clonidine's mechanism of action will be investigated using an adductor canal block (ACB). This is a peripheral nerve block which has been found to be effective in treating postoperative pain after knee alloplastic surgery, with the advantage of being an almost purely sensory block (25-27). The trial will be conducted as a randomized, blinded, paired trial in healthy volunteers. All participants will receive bilateral ACB with 20 mL 0.5% ropivacaine in each thigh. According to the randomization 1.0 mL of clonidine 150 µg/mL will be added to the local anesthetic on one side and 1.0 mL of placebo (normal saline) on the opposite side.

There is a dose response relationship between clonidine and duration of the nerve block. Most studies with positive results have used a clonidine dose of 150 µg.

Nerve blocks are a well-established treatment for surgery and pain relief, and a follow-up study of patients after receiving adductor channel blocks showed no signs of nerve damage 3-6 months after surgery (28). The models used in the study is validated in other medical specialties, and the discomfort experienced is normally only perceived as mild.

A study on isolated sensory neurons from rats showed that clonidine was not associated with increased cell death when used as an adjuvant for ropivacaine (29).

Does Perineural Clonidine Prolong the Duration of an Adductor Canal Block When  
Controlling for Possible Systemic Effects?  
- A Randomized Paired Trial in Healthy Volunteers  
SM1-JH-14, EudraCT 2014-005640-18, VEK nr SJ-437

The aim of the trial is to investigate if clonidine used as an adjuvant to ropivacaine prolongs the duration of a single-shot nerve block by a peripheral mechanism when controlling for systemic effects. Our hypothesis is, that the perineural injection of clonidine as an adjuvant to ropivacaine prolongs the duration of an ACB compared to ropivacaine + placebo.

## Purpose

The purpose of the trial is to investigate whether clonidine used as an adjuvant to ropivacaine prolongs block duration by a peripheral mechanism when controlling for systemic effects. Our hypothesis is that perineural coadministration of clonidine and ropivacaine prolongs the duration of an ACB compared with ropivacaine and placebo.

## Outcomes

### Primary outcome measure

- The difference in duration of sensory block between ACB with ropivacaine + clonidine versus ACB with ropivacaine + placebo, measured as time from block performance (removal of the needle) until an alcohol swab feels cold again (temperature discrimination).

### Secondary outcome measures

- The difference in duration of sensory block between ACB with ropivacaine + clonidine versus ACB with ropivacaine + placebo, measured as time from block performance (removal of the needle) until the stimulation with a needle again elicits a painful response (feels sharp).

# Does Perineural Clonidine Prolong the Duration of an Adductor Canal Block When Controlling for Possible Systemic Effects?

- A Randomized Paired Trial in Healthy Volunteers  
SM1-JH-14, EudraCT 2014-005640-18, VEK nr SJ-437

- The difference in duration of sensory block between ACB with ropivacaine + clonidine versus ACB with ropivacaine + placebo, measured as time from block performance (removal of the needle) until pain during tonic heat stimulation returns to baseline values ( $\pm 10$  mm on a Visual Analogue Scale (VAS)).
- The difference in duration of sensory block between ACB with ropivacaine + clonidine versus ACB with ropivacaine + placebo, measured as time from block performance (removal of the needle) until warmth detection threshold (WDT) returns to baseline values ( $+2^{\circ}\text{C}$  or below).
- The difference in duration of sensory block between ACB with ropivacaine + clonidine versus ACB with ropivacaine + placebo, measured as time from block performance (removal of the needle) until pain heat pain detection threshold (HPDT) returns to baseline values ( $+2^{\circ}\text{C}$  or below).
- The difference in maximum pain score (VAS) during tonic heat stimulation of the skin (30 seconds at  $45^{\circ}\text{C}$ ) between ACB with ropivacaine + clonidine versus ACB with ropivacaine + placebo, at 4 hours post block.
- The difference in maximum pain score (VAS) during tonic heat stimulation of the skin (30 seconds at  $45^{\circ}\text{C}$ ) between ACB with ropivacaine + clonidine versus ACB with ropivacaine + placebo, at 1 hour after resolution of the block (rebound pain).

## Ethical considerations

### General considerations

Ropivacaine is a well-established local anesthetic registered for perineural use, and is administered within recommended doses.

Clonidine is approved for systemic use. Clonidine is not approved for perineural administration, but is well-established in the literature as an adjuvant for peripheral nerve blocks. There are no existing reports of permanent nerve damage in studies employing perineural clonidine, and an in vitro study involving rats did not find increased incidence of nerve inflammation/damage when clonidine was coadministered with ropivacaine compared to ropivacaine alone. It is therefore our opinion that side effects and risks associated with participation in this trial are minimal.

The nerve blocks are performed using ultrasound guidance minimizing the risk of complications. The nerve blocks are performed by one anesthesiologists trained in ultrasound-guided nerve blocks.

The pain-induction model applied in this trial is simple, safe and reproducible.

This trial is conducted in healthy volunteers, since a paired bilateral design is necessary to control for systemic effects.

In this trial, we wish to test the hypothesis that clonidine used as an adjuvant to the ropivacaine in a peripheral nerve block extends the duration of the block by a local mechanism, compared to ropivacaine + placebo. The participants will not benefit directly from the trial, but the results of the trial may become a benefit for patients in the future. We are investigating if clonidine prolongs the duration of a nerve block by a peripheral mechanism. If no

## Does Perineural Clonidine Prolong the Duration of an Adductor Canal Block When Controlling for Possible Systemic Effects?

- A Randomized Paired Trial in Healthy Volunteers  
SM1-JH-14, EudraCT 2014-005640-18, VEK nr SJ-437

effect is seen, then ineffective treatment can be avoided in the future. A demonstrated peripheral effect can lead to a more efficient postoperative pain treatment.

The trial will be conducted according to the Declaration of Helsinki principles. The protocol will be sent to the Regional Ethics Committee, The National Department of Health and the Danish Data Protection Agency. The principal investigator will inform the Regional Ethics Committee, The National Department of Health and the Danish Data Protection Agency in case of significant changes to the protocol. The trial will be registered at <https://eudract.ema.europa.eu> and <https://www.clinicaltrials.gov>.

### Risks, side effects and disadvantages

All procedures, including peripheral nerve blocks, are associated with possible complications, albeit very rarely (0.02-0.4%).

Known complications are:

- Nerve injury (incidence 0.04%). Approximately 99 % of all nerve injuries resolves without treatment within one year.
- Used correctly, no side effects are seen associated with ropivacaine, but upon accidental intravascular injection, serious toxic side effects such as paresthesia, convulsions and circulatory collapse may occur. The risk of intravascular injection of the local anesthetic is minimal, and is reduced by the use of ultrasound and thorough aspiration prior to and after every 5 ml of local anesthetic.
- Systemic side effects of clonidine are transient and often mild. Sedation is normally not perceived as unpleasant. Hypotension (MAP <55) can be treated by administering isotonic saline or ephedrine 10 mg. Bradycardia can occur, but rarely requires treatment. Significant bradycardia of HR<40 can be treated with atropine 0.5 mg iv.
- A small hematoma can occur at the needle puncture site. This may cause tenderness but resolves without treatment.

The nerve blocks will be performed using ultrasound guidance, which probably reduces the risk of complications.

There is a dose response relationship between clonidine and the prolongation of the nerve block. Most studies with positive results used a dose of 150 µg, and at the same time reports a minimum of side effects (30). Clonidine is used frequently daily at the hospital for the treatment of shivering on recovery wards after surgery and opioid abstinence in the ICU. At doses of 300 micrograms, more significant sedation and hemodynamic instability is observed (30).

A peripheral venous catheter is inserted, which rarely leads to a stinging sensation and a small hematoma after removal.

# Does Perineural Clonidine Prolong the Duration of an Adductor Canal Block When Controlling for Possible Systemic Effects?

- A Randomized Paired Trial in Healthy Volunteers  
SM1-JH-14, EudraCT 2014-005640-18, VEK nr SJ-437

A previous trial has shown, that after the performance of an ACB, a minor motor block that will not bother the subject's mobility may be observed(27). The participants will be observed until the block resolves.

It is our opinion, that risks and side effects in relation to this study is minimal, and that participation is associated with very low risk. Participation in this trial is not expected to be associated with any other nuisance, besides the already mentioned above.

## **Informed consent from participants**

The participants will be recruited from the news bulletin for medical students "MOK" in Copenhagen.

The volunteers will be screened in a telephone interview. A copy of the participant trial information will be send prior to the trial date. They will be informed about the possibility of bringing an external assessor. On the trial date, participants will receive oral information by the principal investigator in a closed room without interruptions, in a language understandable to them. Sufficient time for questions will be provided.

## **Data protection**

The trial will be registered at the Danish Data Protection Agency and be conducted in accordance with the data protection policies.

All data will be handled confidentially and all reported data is anonymized. The trial investigators are subject to patient/doctor confidentiality.

The collected data in the form of a Case Report Form and the signed informed consent will only be made accessible for inspection to authorized representatives from the competent authority including members of Good Clinical Practice Unit at the University Hospital Copenhagen.

## **Trial setup:**

### **Timeframe**

The trial is expected to start 01.03.2015.

The trial is expected to end 01.12.2015

Does Perineural Clonidine Prolong the Duration of an Adductor Canal Block When  
Controlling for Possible Systemic Effects?  
- A Randomized Paired Trial in Healthy Volunteers  
SM1-JH-14, EudraCT 2014-005640-18, VEK nr SJ-437

## **Trial location:**

Department of Anesthesiology, Køge Hospital

## **Study design**

|                       |                                                                                                                           |
|-----------------------|---------------------------------------------------------------------------------------------------------------------------|
| Trial type:    | Controlled                                                                                                                |
| Phase:         | Phase 2                                                                                                                   |
| Randomization: | Medicine is prepared by the pharmacy in accordance with a computer-generated randomization list (no block randomization). |
| Blinding:      | Blinded                                                                                                                   |
| Participants:  | Healthy volunteers                                                                                                        |
| Number:        | 21 participants                                                                                                           |

## **Trial Selection**

### **Inclusion criteria**

Participants must meet all of the following criteria in order to be included in the trial:

- Age  $\geq$  18 years
- Participants must understand the protocol fully and sign the written informed consent.
- ASA 1
- BMI  $\geq$  18 to  $\leq$  30
- Male

### **Exclusion criteria**

Participants meeting one or more of the following criteria cannot be included in the trial:

- Participants unable to cooperate in the trial.
- Participants unable to speak or read Danish
- Allergy to study medication.
- Alcohol consumption >21 units per week
- Daily intake of prescription painkillers within the last 4 weeks.
- Over the counter painkillers during the last 48 hours.
- Neuromuscular defects, former surgery or trauma to the lower extremities.
- Diabetes Mellitus
- 2. or 3.rd degree heart block
- Sick sinus node.

# Does Perineural Clonidine Prolong the Duration of an Adductor Canal Block When Controlling for Possible Systemic Effects?

- A Randomized Paired Trial in Healthy Volunteers  
SM1-JH-14, EudraCT 2014-005640-18, VEK nr SJ-437

## Economy

This trial is investigator initiated by clinical research associate professor, MD, Ph.D. [name], Ph.D. [name], Head of department, MD, DMSc, [name] and staff specialist MD [name]. The expenditure related to the trial relates to registration fees, equipment, trial medication and salary for the healthy volunteers. The participants will receive 150 DKK per hour for participating – The amount is taxable. Region Zealand or Region Hovedstaden employs all the involved personnel. The expenditure related to the trial (salary for the participants and trial medication) is covered by a grant from Region Zealand Research Foundation and the department of Anesthesiology University Hospital Zealand, Køge. The investigators have no economic interests regarding the trial.

## Participants completion and interruption of trial

- A participant has completed the trial, when the treatment plan has been followed until one hour after the alcohol-swab again is perceived as cold (normal temperature discrimination).
- A participant who interrupts the trial, is a participant who is included in the trial and has given written informed consent, but has not completed the trial, whether trial medication was given or not. If a participant does not complete the trial, or drops out, a follow-up plan must be stated on if and how data is collected.

## Reasons for trial interruption

A participant can be withdrawn from the trial under the following circumstances:

- A participant is defined as non-responder and withdrawn from the trial if temperature discrimination is present, when stimulated with an alcohol swab in one or both legs 2 hours post block. The participant will be monitored for adverse events for 4 hours after block performance before discharge.
- If the investigator finds it best for the participant.
- If the participant wishes to interrupt the trial.

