Does Perineural Clonidine Prolong the Duration of an Adductor Canal Block When Controlling for Possible Systemic Effects?  
- A Randomized Paired Trial in Healthy Volunteers  
SM1-JH-14, EudraCT 2014-005640-18, VEK nr SJ-437

and forth the tests are done every hour until values are normalized/returned to baseline. If necessary after the first 4 hours there will be given opportunity to sleep and sensory tests as well as blood pressure measurements (if subjects have stabile blood pressure) is omitted here.

- WDT and HPDT are performed at T=1h. If pain score during tonic heat stimulation equals 0 WDT and HPDT are omitted. When pain score during tonic heat stimulation again is > 0, WDT and HPDT are performed every hour until the values have normalized.
- Similarly, temperature discrimination testing with an alcohol swab is performed every half hour if the pain score during tonic heat stimulation is > 0.
- The individual test finishes when the value has returned to baseline.
- A participant is defined as a non-responder and withdrawn from the trial if normal temperature discrimination and pin-prick persists in one or both legs 2h after block performance.
- A block is defined as partial if there is a reduced sensitivity to cold (alcohol swab) and pin-prick, but VAS > 0 tonic heat stimulation at t = 2h.
- Side effects from t=0 until discharge is recorded in the CRF.
- When all values are normalized the trial is terminated and the participant sent home.

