- **Determination of heat-pain threshold (HPDT)** represents the lowest temperature perceived as painful. Start temperature for the thermode is 32 ° C. The temperature rises by 1 ° C/sec during the threshold determination and 5 ° C/sec at the return to the starting temperature after the test. The participant is asked to press a button, when the thermode feels painful while also finishing heat stimulation. If the limit of temperature increase beyond 52 ° C before recording a threshold value the thermode automatically returns to its starting temperature and 52 ° C is recorded. Each threshold value is calculated as the average of four stimulations; stimulations are presented 6-10 seconds apart. The duration of sensory block assessed by HPDT, defined as the time from block performance until HPDT is normalized.

The trial lasts from the introduction until the nerve block wears off (typically 10-14 hours). The participants will receive the above-mentioned treatments according to a computer-generated randomization list.

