### **Guidelines for adverse events and causal relations to treatment**

1. Not related – No temporal relation, other causes more likely.
2. Possibly related – Less clear connection, other causes may also be possible.
3. Probably related – Clear temporal connection with clinical improvement after termination of trial medication, and not reasonably explained by the participants known clinical condition.
4. Related – Clear temporal connection with retesting or clinical assessment.

Participants experiencing adverse events will be monitored with relevant clinical assessments and lab tests according to the treating doctor's decision. All adverse events will be followed until satisfactory restitution or stabilization.

A Serious Adverse Event = SAE is an event that leads to risk of death or handicap for the participant (or their offspring) including, but not limiting to, an event that result in:

- Death
- Life threatening circumstance. Participant was, assessed by the investigator, at apparent risk of death by the adverse event as it occurred.
- Hospital admission
- Permanent invalidation
- Innate anomaly

A product resume for clonidine chapter 4.8 and the product resume for Ropivacaine chapter 4.8 from the department of health homepage as a reference document, when assessing whether a serious adverse event is expected or unsuspected.

Reduced sensitivity and motor deficits are a known effect of nerve blocks and will not be reported to the authorities unless strength and sensitivity is not regained within 36 hours after nerve block. There is a known risk of falling when nerve blocks involves n. femoralis, accordingly falling is not seen as an adverse event unless injury occurs in relation to the fall. The risk of falling is probably lower in relation to adductor channel blocks, all possible precautions will be taken to avoid falls.

Bradycardia, hypotension, sedation and dizziness are also known side effects of clonidine and will not be considered an adverse event.

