## STATISTICAL ANALYSIS

### Sample size calculation

Does Perineural Clonidine Prolong the Duration of an Adductor Canal Block When  
Controlling for Possible Systemic Effects?  
- A Randomized Paired Trial in Healthy Volunteers  
SM1-JH-14, EudraCT 2014-005640-18, VEK nr SJ-437

A few studies have compared the duration of perineural clonidine with systemic clonidine, but these studies have examined combination with bupivacaine(4, 21), mepivacaine(3) and levobupivacaine(22) and not perineural ropivacaine. El Saied (9) investigated ropivacaine with clonidine as an adjuvant perineurally vs. ropivacaine alone in a study with 50 patients. The addition of clonidine as an adjuvant prolonged the sensory blockade 489-628 minutes (95% CI 90-187). In a yet unpublished study by our group on healthy volunteers, we found a sensory duration of an ACB with 20ml ropivacaine 5 mg/ml of 22 (SD 4) hours. Accordingly, we find that a 240 minutes prolongation of block duration will be clinically relevant. With a type 1 error risk of 5% and a type 2 error risk of 10% and an SD of 240 minutes, a total of 18 subjects is needed in this paired trial to show a difference of 240 minutes. In order to compensate for possible dropouts, we plan to include 21 participants.

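### A participant withdrawn because one block failed may be discharged after 4 h of monitoring while the other leg is still blocked, which conflicts with the promise of observation until the block resolves

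*Protocol*

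**What the plan says.** All references are to the Protocol.

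- **Reasons for trial interruption.** A participant is a non-responder and is "withdrawn from the trial if temperature discrimination is present, when stimulated with an alcohol swab in one or both legs 2 hours post block". The next sentence reads: "The participant will be monitored for adverse events for 4 hours after block performance before discharge".
- **Trial schedule for the participants.** The same event is described with a different test requirement but the same laterality: "withdrawn from the trial if normal temperature discrimination and pin-prick persists in one or both legs 2h after block performance". Every participant receives a block in each leg. Side effects are entered in the case report form from block performance up to discharge. The list closes with: "When all values are normalized the trial is terminated and the participant sent home".
- **Risks, side effects and disadvantages.** After noting that a minor motor block may occur, the protocol states: "The participants will be observed until the block resolves". No exception is made for withdrawn participants.
- **Participants completion and interruption of trial.** For anyone who does not complete, the protocol calls for a plan setting out whether and how data will be gathered.
- **Expected duration.** Under Sample size calculation: "we found a sensory duration of an ACB with 20ml ropivacaine 5 mg/ml of 22 (SD 4) hours". The end of the Sensory tests section gives a typical figure of 10-14 h.

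**The concern.** The non-responder rule is triggered by failure in one leg. A participant with one failed and one working block is withdrawn at 2 h, and the only discharge statement that names withdrawn non-responders attaches 4 h of adverse-event monitoring to them. The other leg is still blocked at that time and may have received clonidine, which the protocol itself says is not approved for perineural use.

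Two things are at stake. First, a site that takes 4 h as the discharge time acts against the risk section's statement that participants are observed until the block resolves. Second, recording of side effects stops at discharge, so the return of sensation in the working leg would not be documented for this participant, although it would be for a completer. The point concerns safety observation and its record. How non-responders are defined or analysed is a separate matter.

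**Working it through.** There is no design figure to reproduce. The check has two parts: who falls under the rule, and whether a working block can be expected to outlast 4 h.

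**1. Who falls under the rule**

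| State at 2 h | Withdrawn? | Block left? | Conflict with observation until resolution? |
|---|---|---|---|
| Both blocks failed on every test | Yes | No | No |
| One failed, one working | Yes (one leg is enough) | Yes, other leg | Yes, if 4 h is the discharge time |
| Both working | No | Yes | No; participant stays until values normalise |

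Only the middle row is at issue. One of the two non-responder definitions asks for cold sensation alone and the other for cold and pin-prick. They may therefore withdraw different people, but both include the middle row.

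**2. Block remaining at 4 h**

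Inputs: duration 22 h with SD 4 h (Sample size calculation); typical duration 10-14 h (end of Sensory tests); monitoring 4 h (Reasons for trial interruption).

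Remaining block = expected duration − 4 h:

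- 22 − 4 = 18 h
- 10 − 4 = 6 h and 14 − 4 = 10 h

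The 10-14 h figure is worded as the length of the trial from the introduction, so the block itself would be somewhat shorter and 6-10 h is slightly generous.

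Chance that a working block has already resolved at 4 h, assuming normally distributed durations: P(duration < 4) = Φ((4 − mean)/SD).

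- Mean 22, SD 4: Φ(−18/4) = Φ(−4.5), about 3 in a million
- Mean 10, SD 4: Φ(−6/4) = Φ(−1.5), about 7%
- Mean 14, SD 4: Φ(−10/4) = Φ(−2.5), about 0.6%

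The SD of 4 h is stated only with the 22 h mean; its use with 10 h and 14 h is an assumption. The two duration figures disagree with each other, which is a separate matter, but on either one the working block is expected to be present at 4 h.

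**3. What is recorded afterwards**

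Side effects are recorded until discharge. The completion section requires a follow-up plan for non-completers. The section on reasons for interruption gives only the 4 h of monitoring, and the section on the withdrawal procedure only says that the reason for withdrawal is noted. Neither says how recovery of a still-blocked leg is established.

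**4. How many participants**

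The sample size section plans 21 participants where 18 are needed, an allowance of 21 − 18 = 3 for dropouts of any kind. Nothing says how many of these would be one-sided failures, so the frequency cannot be derived.

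**The case against.** The strongest reply is that 4 h is a minimum. The sentence says monitoring takes place before discharge; it does not say that discharge takes place at 4 h. The same 4 h applies to ECG, oximetry and blood pressure in every participant. A site that monitors for 4 h and then observes until the block resolves would satisfy both passages. This reading is possible, so the text is not impossible to follow. But the sentence does not say it is a minimum, and the risk section does not say it admits an exception. The ambiguity stands.

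The completion section already demands a follow-up plan for non-completers, and the adverse-event guidelines follow events until recovery or stabilisation. The first of these means it cannot be asserted that recovery will be unknown; it will be undocumented only if the plan is silent on it. The second applies to events that have already been detected.

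Three stronger readings are tempting and are not supported:

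- A reader might infer a further contradiction with "When all values are normalized the trial is terminated and the participant sent home". That line closes the schedule for participants who stay in the trial; the same list withdraws non-responders a few lines earlier.
- A reader might infer that 32 of 36 h (36 − 4) of required observation is lost. The 36 h in the adverse-event sections decides what counts as an adverse event and what is reported. It sets no observation period for anyone, and on either duration figure completers would usually go home before 36 h as well.
- A reader might cite "There is a known risk of falling when nerve blocks involves n. femoralis" as showing a serious fall hazard. The same paragraph says the risk is probably lower with this block. Elsewhere the block is described as almost purely sensory, and any motor effect as minor and no hindrance to mobility.

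**Conclusion.** The point holds in limited form. For a participant with one failed and one working block, the 4 h monitoring statement, read as the discharge time, contradicts the unqualified statement that participants are observed until the block resolves. About 18 h of block (22 h figure) or 6-10 h (10-14 h figure) would remain. That conclusion needs only that the expected duration exceeds 4 h, which both figures satisfy; the tail probabilities also rest on normality and, for the shorter figure, on a borrowed SD.

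Documentation of recovery in that leg depends on a follow-up plan that the protocol requires but does not state for this case. The number of participants affected is unknown, those whose blocks failed in both legs are outside the point, and the primary estimate is unaffected. Should be fixed: it touches participant safety and a risk statement about healthy volunteers, but it does not threaten the trial's result.

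**What to change.** Reconcile the non-responder paragraph under Reasons for trial interruption with the observation statement under Risks, side effects and disadvantages, and with the follow-up requirement under Participants completion and interruption of trial. The result should be one stated criterion for discharge and safety follow-up that expressly covers a withdrawn participant who still has a working block in the other leg. It should make clear whether 4 h is a minimum or the discharge time, and how recovery of the blocked leg is documented. Which criterion to adopt is a clinical decision for the sponsor and is not proposed here.

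The cost is protocol wording, plus whatever follow-up the sponsor specifies for the few participants it may concern. Randomisation, sample size and analysis do not change.
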